# Protocol outline

**Title of Study**: A Single Center Pilot Study to Determine Diagnostic Performance of 64 Slice CT Angiography in Emergency Department Patients with Chest Pain for Differentiation of Cardiac Causes from Aortic Dissection, Pulmonary Embolism, or other Non-cardiac Causes of Acute Chest Pain using GE LightSpeed VCT^TM^

**Acronym:** ACUTE CT Trial (Assessment of Acute Chest Pain Utilizing a Triple Rule Out Evaluation by CT).

**Rationale:**

Acute chest pain is a common and costly clinical condition accounting for over 5 million emergency department visits per year in the United States. In general, individuals presenting to the emergency department for chest pain require 6-24 hours of observation and multiple tests to differentiate pain from blocked heart arteries (i.e., acute or chronic coronary syndrome) from other non-cardiac sources.

Patient evaluation for cardiac causes typically includes sequential electrocardiograms and blood tests for heart enzymes to establish if a heart attack has occurred. Subsequently, cardiac stress testing or heart catheterization is required to firmly establish a diagnostic and treatment plan.

Non-cardiac but potentially life threatening illnesses can mimic cardiac symptoms and make an accurate diagnosis difficult, including a) blood clots in the lung vessels, or pulmonary embolism (PE), or b) a tearing of the vessel wall in the large artery supplying oxygenated blood to the body known as aortic dissection. These diagnoses are missed initially in the Emergency Room in up to 10% of patients presenting with acute chest pain. Failure to recognize these diseases often leads to delayed, unwarranted, or even detrimental medical treatments for these patients. Other non-cardiac causes of acute chest pain may include pneumonia, pleurisy, rib or other bone fracture, neuritis, or soft tissue injury.

Ideally, management of patients with acute chest pain would include a single test that is fast, easy to administer, widely and readily available at all times, and able to effectively differentiate many causes of acute chest pain. However, no single test currently exists.

CT is a widely available and standard imaging tool in Emergency Department (ED) that has been used for imaging applications throughout the body. CT angiography has been well studied and validated for identifying PE and aortic dissection when suspected, and is the preferred imaging modality for these diseases. Use of CT allows effective and timely evaluation for each of these potentially lethal diagnoses. CT can also effectively diagnose pneumonia, fracture, soft tissue injury, and may show signs suggesting pleurisy or neuritis. However, technical difficulties in imaging the moving heart and the size and motion of the small heart arteries (typically 4 to 1.5 mm and smaller) have been daunting for CT imaging.

Recent rapid advancement of multislice CT technology has allowed faster scanning times, better image resolution, and less intravenous contrast for visualization of structures. CT angiography holds the promise of enabling a non-invasive evaluation of the small coronary arteries that supply the heart. Four, 8, and 16 slice CT scanners have been used to imaging coronary arteries but poor spatial resolution and blooming artefact off calcified atherosclerosis has resulted in a significant number of coronary segments (up to 35% with 16 slice) that could not be evaluated using these scanners.

General Electric Healthcare has developed an innovative LightSpeed VCT. With the VCT scanner, 64-channels worth of data can be acquired in a single rotation, which allows cardiac CT data acquisition to be accomplished in the range of 5 seconds or 5 heart beats.

The newer, faster CT machine allows evaluation of coronary anatomy as well as atherosclerotic blockages with image resolution that approximates that of invasive coronary catheterization, the current gold standard test for coronary artery disease. **T**he 64 slice CT as an evaluation tool for patients presenting at ED with acute chest pain but with low to intermediate risk for angina would potentially allow rapid triage patients to 1) implement appropriate treatments, 2) ensure discontinuation of potentially harmful treatments, and 3) limit observation time and diagnostic testing in the acute setting.

In the ACUTE CT study, we propose using VCT as a first line imaging modality to evaluate patients presenting with acute chest pain in ED.

The hypothesis of the study is that

1. in low to intermediate CAD risk patients presenting with acute chest pain in ED, VCT examination will be able to exclude obstructive CAD as a cause for cardiac chest pain compared to routine evaluation and to accurately diagnose non-cardiac causes of acute chest pain by detecting presence of pulmonary embolus, aortic dissection, or other causes of chest pain.
2. the findings of VCT examination are able to accurately triage patients for proper management strategy
3. VCT examination will be able to reduce cost of and time required for managing patients with acute chest pain.

**Primary Objective:** To evaluate the diagnostic performance of VCT for differentiation of cardiac from non-cardiac causes of acute chest pain in ED to determine presence or absence of 1) significant blockages in the coronary arteries that supply the heart, 2) evidence of dissection of the aortic tissues, and 3) obstructive blood clots in the pulmonary arteries when compared to standard care information.

**Secondary Objectives:**

- To evaluate impact of the VCT findings on patient management.
- To evaluate the cost of VCT for determining the aetiology of acute chest pain when compared to the standard care.

**Number of Subjects Planned:** 150

**Inclusion Criteria:** Subjects may be included in the study if they meet all of the following criteria:

**Inclusion Criteria**

- Male: 30-75 years old or Female: 45 -75 years old
- Acute chest pain onset within 24 hours
- No obvious cause for chest pain
- Low to intermediate risk of myocardial ischemia by TIMI Unstable Angina Score (<5)
- One or more cardiac risk factors
  - Hypertension
  - Dyslipidemia
  - Diabetes
  - Family history – 1^st^ degree relative with CAD or cardiac event less than age 55 years
  - Current or recent smoker (<1 month)
  - Morbid obesity but BMI≤40
  - Sedentary lifestyle
- Able and willing to comply with study procedures and signed and dated informed consent
- For a female patient, she must be either surgically sterile (has had a documented bilateral oophorectomy and/or documented hysterectomy), or post-menopausal (cessation of menses for more than 1 year), or if of childbearing potential the results of a serum or urine human chorionic gonadotropin pregnancy test, performed within 36 hours of administration, must be negative.

**Exclusion Criteria:** Subjects must be excluded from participating in this study if they meet any of the following criteria:

1. Has known allergies to iodinated contrast agent, including but not limited to anaphylactoid or cardiovascular reactions, laryngeal edema, or bronchospasm
2. ST segment elevation or dynamic ST changes on ECG
3. Elevated cardiac enzymes (troponin I >2 mg/dl, CK-MB index > 9%)
4. Has atrial fibrillation/flutter or any irregular heart rhythm considered by the investigator to interfere with temporal acquisition of cardiac CT images.
5. Creatinine level >1.8 mg/dl
6. Pregnant or lactating female
7. Hemodynamic or respiratory instability as determined by the ED physician
8. Clinically active, serious, life-threatening disease with a life expectancy of less than 2 months.
9. Not willing/unable to discontinue metformin (eg, Glucophage^®^) at the time of the study procedure. Metformin must be withheld for at least 48 hours post-procedure and be restarted only after the subject’s renal function has been evaluated and it is deemed safe to resume metformin.
10. Previously included in this study.
11. Received a non-FDA approved drug within 30 days prior to the administration of the investigational product, or is scheduled to receive one during the administration of the investigational product, or within 72 hours afterward.
12. Moderate to severe reactive airway disease requiring >1 inhalor or prednisone or patient is actively wheezing on physical examination.

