**Study Design:**

This study is designed as a single-centre trial to determine diagnostic value of VCT for differentiating cardiac from non-cardiac causes of acute chest pain in ED. Approximately 150 patients will be enrolled over a period of approximately 15 months.

The patient enrolment and study procedures are illustrated in the study flow charter, Figure 1.

Figure 1: Study Flow charter

Patients with acute chest pain presenting in ED

Initial Management by ED staff

- Clinical history
- ECG
- Chest X-ray
- IV line establishment and routine blood draw
- Medical therapy initiated

No or patient refuse

Standard care

No patient F/U

Eligible for enrollment?

Yes and patient consent

- Detailed history by research staff
- Additional blood for testing
- CT data available for clinical use when it is clinically needed
- The axial images and reconstructed image sets will be sent to core-lab for blinded evaluation

VCT scan

Two consensus readers review all clinical information and make diagnosis

- Routine care by primary physicians
- Additional imaging or lab tests
- Collection of medication, discharge diagnoses and cost information

Patient follow-up

**Study Imaging Tests:** Chest CT and cardiac CTA.

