**Secondary Efficacy Endpoint(s):**

- Accuracy of VCT findings for triage patients to 1) implement appropriate therapy, 2) discontinue unnecessary/potentially harmful treatments, 3) limit observation time and diagnostic testing in the ED setting for acute chest pain.
- Potential cost saving using VCT to determine the aetiology of acute chest pain when compared to the standard care by changing patient management strategy.

**Safety Variables:** The following safety data will be collected and evaluated through the CT procedure:

- Unexpected adverse events
- Serious adverse events

**Gold Standard/Standard of Truth/Truth Panel:** Routine clinical information, including but not limited to, medical history, laboratory tests, ECG tests, other image tests and non-cardiac CT findings. To arrive at an adjudicated diagnosis, two board certified cardiologists independently reviewed all available evidence including history and physical, chest radiograph, non-cardiac CT findings, ECG’s, stress tests, cardiac catheterization, clinical follow up, and pharmacologic trials. Patients were categorized as ACS in the adjudicated diagnosis if 1) plasma troponin I >0.4 mg/dL during the index hospitalization, 2) a nuclear stress test with a summed difference score > 3, 3) an echocardiographic stress test with new or worsening dyssynergy in at least 1 ventricular segment, or 4) coronary stenosis >70% on catheterization. Each reviewer generated a prioritized adjudicated diagnosis list for each patient after the 3 month follow up data were available. Discrepancies between the reviewer’s lists were resolved by consensus. The highest priority consensus diagnosis was considered the cause of the patient’s symptoms for data analysis.

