**Statistical Methods:** The primary outcome is the diagnostic performance of CT compared to the standard of care to diagnose acute coronary syndrome (ACS). The classification accuracy of coronary CT to an adjudicated diagnosis for ACS. The diagnostic measures (e.g., sensitivity, specificity) for the CT diagnostic test for “significant CAD” (>50% stenosis) will be determined using the adjudicated diagnosis for ACS as the correct diagnosis. A >70% CTA stenosis will also be tested as a binary variable. Empiric confidence intervals will be calculated for each point estimate. Receiver operator classification (ROC) curves and area under the curve (AUC), both binary and empiric, will also be calculated. Classification accuracy between ECG-gating techniques (i.e., P-CT and R-CT) will be compared by relative probability estimates.

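### Exclusion 3 admits troponin I up to 2 mg/dl while the reference standard counts any value above 0.4 mg/dL as ACS, so patients who already meet an ACS criterion before CT can enter the accuracy sample

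*Protocol*

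**What the plan says.** The Protocol sets two numerical limits for troponin I, in the same written unit.

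- **Entry (Exclusion Criteria, item 3).** The excluded group is "Elevated cardiac enzymes (troponin I >2 mg/dl, CK-MB index > 9" percent. A value up to and including 2 does not exclude.
- **Reference standard (Gold Standard/Standard of Truth/Truth Panel).** "Patients were categorized as ACS in the adjudicated diagnosis if 1) plasma troponin I >0.4 mg/dL during the index hospitalization". Three other criteria follow, the last being "or 4) coronary stenosis >70% on catheterization". They are alternatives, so troponin alone suffices. The same paragraph has two cardiologists draw up prioritized diagnosis lists after the 3-month follow-up and takes the highest-priority consensus diagnosis for analysis.

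Statistical Methods says that the accuracy of "the CT diagnostic test for “significant CAD” (>50% stenosis") "will be determined using the adjudicated diagnosis for ACS as the correct diagnosis". The Primary Efficacy Endpoint section names predictive values.

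On timing, the flow chart in Study Design lists "IV line establishment and routine blood draw" under initial management, before the eligibility decision and the scan. Laboratory Analysis has troponin I measured every 8 hours.

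Hypothesis 1, in the Rationale, is that "in low to intermediate CAD risk patients presenting with acute chest pain in ED, VCT examination will be able to exclude obstructive CAD".

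**The concern.** The entry rule and the truth rule use the same blood marker but disagree on which values count as positive. A patient in the gap between the limits is treated as not elevated at entry, and may then be counted as an ACS case on that same result.

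The study asks whether CT can sort out chest pain in patients of low to intermediate risk. A patient who already meets the protocol's ACS definition on routine blood work contributes a case that CT was not needed to find. If enough such patients enter, sensitivity and the predictive values become a mixture of two groups, and the reader cannot tell how CT performed in those whose status was still open. With few ACS cases expected among 150 patients, a handful could form a large share of the sensitivity denominator.

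**Working it through.** **Step 1: apply both rules to test values** (exclude if above 2; ACS criterion 1 if above 0.4).

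| Troponin I before CT | Entry | ACS criterion 1 |
|---|---|---|
| 0.40 | eligible | not met |
| 0.41 | eligible | met |
| 1.0 | eligible | met |
| 2.0 | eligible | met |
| 2.01 | excluded | met |

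The overlap is above 0.4 and up to 2. The limits differ by 2 / 0.4 = 5-fold. The enzyme limits in exclusion 3 are joined only by a comma; if both had to be exceeded, the overlap would be wider.

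**Step 2: look for another rule that closes the gap.** The inclusion criteria ask for no obvious cause of the pain and a TIMI score below 5. Neither states a troponin value. No section analyses these patients separately.

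**Step 3: timing.** Exclusion 3 cannot be applied without an entry troponin, so the relevant value exists before the scan. Criterion 1 covers the whole index hospitalization and is not confined to values after CT.

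**Step 4: size, by illustration.** The Protocol gives no ACS prevalence, expected accuracy or troponin distribution, so there is no planned figure to reproduce. All inputs here are assumptions except N = 150: 15 ACS cases not evident at entry, CT sensitivity 80% in them; k = 2, 5 or 8 further cases already above 0.4 at entry, CT sensitivity s in them.

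Pooled sensitivity = (0.80 × 15 + s × k) / (15 + k). Prevalence = (15 + k) / 150, against 15 / 150 = 10.0%.

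| k | s = 70% | s = 90% | s = 100% | Prevalence |
|---|---|---|---|---|
| 2 | 13.4/17 = 78.8% | 13.8/17 = 81.2% | 14/17 = 82.4% | 17/150 = 11.3% |
| 5 | 15.5/20 = 77.5% | 16.5/20 = 82.5% | 17/20 = 85.0% | 20/150 = 13.3% |
| 8 | 17.6/23 = 76.5% | 19.2/23 = 83.5% | 20/23 = 87.0% | 23/150 = 15.3% |

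Pooled sensitivity therefore lies above or below 80% according to s, which the Protocol does not give.

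**Step 5: predictive values.** Assume also 90% specificity, so false positives = 0.10 × (135 − k).

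- Positive predictive value (PPV) with s = 100%: 14/27.3 = 51%, 17/30 = 57% and 20/32.7 = 61% for k = 2, 5 and 8. Without these patients: 12/25.3 = 47%, 12/25 = 48% and 12/24.7 = 49%.
- Negative predictive value (NPV) does not move when s = 100%. With s = 70% and k = 8, true negatives are 0.90 × 127 = 114.3 and false negatives 3 + 2.4 = 5.4. NPV is then 114.3/119.7 = 95.5%, against 114.3/117.3 = 97.4% without them.

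A patient added as an ACS case can only raise PPV or leave it, and only lower NPV or leave it. If the consensus diagnosis makes that patient a non-case, both effects reverse.

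**The case against.** The strongest reply is that the two limits do different jobs. One screens at entry; the other classifies over the whole stay. A troponin that first passes 0.4 after the scan marks a legitimate case that CT should find. This stands, and it confines the point to values already above 0.4 before CT.

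A reader might infer more than the documents support:

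- **That such patients do enter.** The Protocol gives no count. Clinical judgement under the no-obvious-cause criterion may remove some or all of them. What can be said is that no numerical rule does so.
- **That the truth label is settled before the scan.** Criterion 1 is worded without conditions, but the analysis uses the highest-priority consensus diagnosis. A patient with troponin above 0.4 and a different leading diagnosis, such as pulmonary embolism, may not be analysed as ACS.
- **That sensitivity is inflated.** This follows only if CT sensitivity in the added cases is assumed to be higher than in the rest. At 70% it falls to 79%, 78% or 77%.
- **That this is incorporation bias.** Troponin is no part of the CT result, so it is not.
- **That the results no longer describe the intended patients.** Hypothesis 1 speaks of low to intermediate risk, which the inclusion criteria define by TIMI score; it does not say undiagnosed. The sample would be a broader spectrum, not a different population.

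It is also fair that the sensitivity shifts, at most 7 points here, are small beside the sampling error: the exact 95% interval for 12/15 is 52% to 96%. And this is a single-centre pilot with no stated performance threshold. Finally, a statistical analysis plan that is not shown might split the analysis set. That would limit the damage, but the Protocol's two limits would still disagree.

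**Conclusion.** The point holds in a limited form. The Protocol's limits leave a band, above 0.4 and up to 2 mg/dL, in which a patient is eligible and already meets a sufficient ACS criterion before CT. That follows from the text and needs no assumption. The consequence is a mixed case spectrum and a higher ACS prevalence in the primary accuracy figures; accuracy against the adjudicated label can still be calculated.

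The size rests wholly on assumed inputs. With 15 other cases at 80% sensitivity and 2 to 8 added cases at 70% to 100%, pooled sensitivity is about 77% to 87%, and prevalence is 11.3% to 15.3% in place of 10.0%. If 90% specificity is also assumed and CT finds every added case, PPV is 4 to 12 points higher with them than without. The number affected could be zero, and neither the size nor the direction of the net effect can be fixed from the Protocol.

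It might be inferred that the entry limit ought to be lowered to 0.4. The documents do not show which of the two limits is right, and this point does not depend on it.

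**What to change.** 1. Reconcile the troponin I limits in exclusion criterion 3 and ACS criterion 1, or state why they differ. Which limit applies is for the investigators to settle.
2. Define the primary accuracy set as patients whose last troponin before CT does not already meet criterion 1 as finally stated.
3. Report patients who already meet it in a separate row, with their number, CT result and adjudicated diagnosis.
4. Give results for all enrolled patients as a sensitivity analysis.
5. State that values first exceeding the limit after the scan remain cases in the primary set.

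The cost is a few sentences, and the troponin values are already collected. The Gold Standard paragraph is written in the past tense; if enrolment and adjudication are complete, a changed entry limit cannot help, but items 2 to 5 still can.

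The downside is fewer ACS cases in the primary set and a somewhat wider interval. For example, with 5 of 20 cases moved to the separate row, an exact (Clopper-Pearson) 95% interval of 62% to 97% for 17/20 becomes 52% to 96% for 12/15.

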**Study Design:**

This study is designed as a single-centre trial to determine diagnostic value of VCT for differentiating cardiac from non-cardiac causes of acute chest pain in ED. Approximately 150 patients will be enrolled over a period of approximately 15 months.

The patient enrolment and study procedures are illustrated in the study flow charter, Figure 1.

Figure 1: Study Flow charter

Patients with acute chest pain presenting in ED

Initial Management by ED staff

- Clinical history
- ECG
- Chest X-ray
- IV line establishment and routine blood draw
- Medical therapy initiated

No or patient refuse

Standard care

No patient F/U

Eligible for enrollment?

Yes and patient consent

- Detailed history by research staff
- Additional blood for testing
- CT data available for clinical use when it is clinically needed
- The axial images and reconstructed image sets will be sent to core-lab for blinded evaluation

VCT scan

Two consensus readers review all clinical information and make diagnosis

- Routine care by primary physicians
- Additional imaging or lab tests
- Collection of medication, discharge diagnoses and cost information

Patient follow-up

**Study Imaging Tests:** Chest CT and cardiac CTA.

**CT Imaging Procedures:**

***Figure 2*** Outlines the CT scanning protocol.

*N*TG = nitroglycerin

*Subject preparation*

- Explain the test to the subject.
- Position the subject supine on the CT table with feet first.
- If the heart rate is >70 bpm, an IV bolus of metoprolol 2.5-5mg IV or oral dose of 100 mg PO metoprolol is given and repeated to achieve a heart rate <65 or until hypotension (systolic blood pressure <100 mmHg or the patient has lightheadedness or symptoms of hypoperfusion) limits further treatment
- A single dose of nitroglycerin of 0.4 mg given sublingually will be administered just prior to entering the CT gantry to dilate the coronary arteries for imaging if SBP > 100 mmHg
- Instruct and practice proper breath-holding with the subject using hyperventilation (take a breath in, blow the air out, take another breath in, blow the air out, and take a final breath in and hold the breath) and take note of the heart rate while they are holding their breath (oxygen can be given to the subjects who have difficulty holding their breath).

*ECG Leads and Power Injector Connection*

ECG leads should be placed in the appropriate location with firm connection. The subject’s arms must be raised above the head in order to appropriately position the leads: black – left chest below clavicle, white – right chest below clavicle, red – left abdomen below 6^th^ rib, and green – right abdomen below ribs (if it is available).

To confirm a good connection, check the ECG tracing on the monitor on the scan console.

Visipaque 320 mg-I/mL will be administered via power injector. Load power injector with 120 mL of the contrast agent. Approximately 70 mL saline must be loaded in the second barrel. The power injector must be securely connected to the subject’s IV line.

*Calcium Scan*

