**CT Image Evaluation/Procedures*:***

Two blinded readers who are qualified by their clinical training will be selected for evaluation of the CT images independently. All blinded reviewers must have no financial conflict. The independent image evaluation will be performed at a central imaging core-lab. Planar, cross sectional non-contrast and contrast CT images are compiled for analysis using GE AW 4.2 or higher workstation.

- Cross sectional, longitudinal, and curved planar CTA images will be reconstructed. Multiplanar images are created and reconstructed into a 3 dimensional rendering using the GE algorithms.
- Non-cardiac causes of acute chest pain will be evaluated and recorded, including pulmonary embolus, aortic dissection, lung parenchyma abnormalities, mediastinal abnormalities, other aortic abnormalities, rib fracture, pleurisy, etc.
- Coronary calcium scoring is calculated by the Agatston method, as well as volumetric and mass measurements.
- A 21 segmental ACC/AHA model of the coronary tree will be used for the coronary evaluation.
- For the coronary evaluation, two independent readers must review at least 10 imaging segment phases of images to determine:
- Overall image quality from single best phase for each of the 15 coronary segments in vessels 1.5 mm in diameter or larger.
- Coronary artery supply dominance and coronary anomalies
- Coronary artery segmental interpretability and vessel size down to 1.5 mm
- Presence or absence of coronary artery stenosis/occlusion
- Presence or absence of coronary plaque and characterizing vessel segment plaque as non-calcified, mixed, and calcified or combinations thereof. Non-calcified is defined as less than 40 HU, mixed is 40-150 HU, calcified is greater than 150 HU. A single lesion will be chosen for HU measured: that lesion showing greatest degree of negative or positive remodeling. Further, the segment extent of involvement will be visually graded as trace plaque (less than 10% of length of the vessel segment involved), mild plaque (10-25%), moderate (25-50%), or severe (50-100%).
- If a coronary stenosis >30% is suspected, CT quantitative coronary angiography analysis (QCA) is performed on the lesion to calculate minimal vessel lumen diameter and luminal area. Percent stenosis is calculated based on the proximal coronary considered non-significantly diseased divided into the minimal diameter and area of the lesion.

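### Nitroglycerin before the scan depends on systolic pressure alone, so a patient whom the metoprolol rule counts as hypotensive on symptoms is still directed to receive it

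*Protocol*

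**What the plan says.** Two consecutive bullets under CT Imaging Procedures, Subject preparation, set the conditions for two drugs that can lower blood pressure.

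- **Metoprolol.** When the heart rate exceeds 70 bpm, the drug is given intravenously (2.5 to 5 mg) or by mouth (100 mg). Doses continue towards a rate below 65, with this limit: "until hypotension (systolic blood pressure <100 mmHg or the patient has lightheadedness or symptoms of hypoperfusion) limits further treatment".
- **Nitroglycerin.** "A single dose of nitroglycerin of 0.4 mg given sublingually will be administered just prior to entering the CT gantry". The purpose and the only stated condition follow: "to dilate the coronary arteries for imaging if SBP > 100 mmHg".

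Two other places bear on the point. Exclusion criterion 7 keeps out patients with "Hemodynamic or respiratory instability as determined by the ED physician". The same imaging section opens by referring to Figure 2, which "Outlines the CT scanning protocol" and whose legend spells out the abbreviation for nitroglycerin. The figure itself is not legible in the copy reviewed.

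**The concern.** The metoprolol bullet does not rely on the pressure reading alone. It joins the pressure limit and the symptoms with an *or*, so lightheadedness or signs of poor perfusion count as hypotension at any pressure. The nitroglycerin bullet, for the next drug in the same preparation sequence, keeps the pressure limit and drops the symptoms. Its wording is directive: the dose is to be given when the pressure condition is met.

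A patient who becomes symptomatic after metoprolol, and still is when the nitroglycerin is due, can therefore be hypotensive under one bullet and due a vasodilator under the next. At this step the drug serves the images and does not treat the patient. Under CT Image Sequestering and Data Release, the cardiac findings are also withheld from the treating physicians. The risk of the dose therefore has little direct clinical return for that patient, which argues for the more cautious condition.

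**Working it through.** The plan gives no figure to reproduce here. The check is a logical comparison of the two rules, applied at the moment nitroglycerin is due.

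**Inputs** (both from CT Imaging Procedures, Subject preparation)

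- Metoprolol limit reached: SBP < 100 mmHg, or lightheaded, or symptoms of hypoperfusion.
- Nitroglycerin given: SBP > 100 mmHg.

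**The four states**, with *symptoms* meaning lightheadedness or hypoperfusion symptoms at that time:

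| SBP | Symptoms | Metoprolol limit reached | Nitroglycerin as written | Nitroglycerin with symptom clause |
| --- | --- | --- | --- | --- |
| < 100 | present | yes | withheld | withheld |
| < 100 | absent | yes | withheld | withheld |
| > 100 | present | yes | **given** | withheld |
| > 100 | absent | no | given | given |

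- States that count as hypotension under the metoprolol rule: 3.
- States in which nitroglycerin is withheld as written: 2.
- Difference: 3 − 2 = 1, the state with SBP above 100 mmHg and symptoms present.
- With the symptom clause added, nitroglycerin is withheld in 3 states, so the difference is 3 − 3 = 0. A patient who has recovered (SBP above 100, no symptoms) is still dosed.

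**Boundary.** At exactly 100 mmHg nitroglycerin is withheld under either wording, because 100 is not above 100. Without symptoms, the metoprolol limit is not reached at that value. The two rules therefore also differ there, but in the cautious direction.

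**Other limits on nitroglycerin.** No other legible part of the Protocol adds a symptom hold, a re-check after metoprolol or another contraindication. Exclusion criterion 7 is an eligibility judgement and does not address symptoms that appear after the beta-blocker.

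**The case against.** Five arguments can be made for leaving the text as it is.

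1. **Figure 2 may already contain the condition.** Its legend mentions nitroglycerin, so it probably shows that step, and an illegible figure must not be treated as a gap in the plan. This stands as a limit: the point applies to the bullet and not necessarily to the whole protocol. If the figure does carry a symptom hold, the bullet should still agree with it.
2. **The metoprolol bullet limits further *treatment*, which could include nitroglycerin.** On that reading there is no gap and the change is editorial. The narrower reading is more natural, because the phrase ends the repeated metoprolol dosing and nitroglycerin has its own condition. The broad reading cannot be excluded.
3. **Two drugs need not share hold criteria.** That is true in general, and the bullets do not contradict each other formally. But the Protocol itself classes these symptoms as hypotension, and it gives no reason for disregarding them before a vasodilator.
4. **Clinical staff would withhold the dose anyway.** Probably so, which is why the point is minor. It does not change what the written instruction directs.
5. **The frequency is unknown and no planned analysis is affected.** Both are correct, and neither is claimed otherwise.

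**Conclusion.** The concern holds for the legible text, as a minor point. Followed literally, the nitroglycerin bullet directs an imaging-only vasodilator to a patient whom the preceding bullet counts as hypotensive. The unsafe divergence is confined to one of the four states: symptoms still present with SBP above 100 mmHg. It does not extend to patients whose symptoms have resolved. The number affected among the 150 planned patients is unknown and is not estimated.

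The conclusion rests on two assumptions: that Figure 2 does not already supply the condition, and that the limit on further treatment refers to metoprolol. If either fails, what remains is a matter of clearer wording. Confidence is moderate for that reason.

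**What to change.** Extend the condition in the nitroglycerin bullet so that the dose is given only if SBP is above 100 mmHg **and** the patient has neither lightheadedness nor symptoms of hypoperfusion at that time. Patients who reached the metoprolol limit earlier but have recovered may still be dosed. Check that the nitroglycerin step in Figure 2 carries the same condition.

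Optionally, record each withheld dose with its reason, so that scans done without dilation can be identified in the analysis.

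The cost is one clause and, if the record is wanted, one data field. The drawback is that a few scans would be done without coronary dilation. That may make small segments harder to read, and the CT Image Evaluation/Procedures section has the readers assess "Coronary artery segmental interpretability and vessel size down to 1.5 mm". The Protocol gives no figure for the size of that effect.
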